### Craving-Manager app

2.7.

The Craving-Manager app was developed by SANPSY lab at University of Bordeaux, Bordeaux, France. According to the Cue-Craving-Use model of addiction proposed on the basis of previous EMA research (7, 37), this trans-addiction app was designed to anticipate, monitor and help the participants to cope with cues, craving and addictive use, whatever the substance or the behavioral addiction. The app covers all the addictions already (or waiting to be) acknowledged by the DSM (including tobacco, alcohol, cannabis, opiates, cocaine, crack, stimulants, sedatives, gambling, gaming) but also covers other potential addictions, including food, shopping/spending, exercise, work, sex/pornography, trading, smartphone/SMS, Social network/chat, television, online dating, stealing/ kleptomania, and an open-response item has been added for any other use/addictive behavior for which the participant feels a loss of control/ need for treatment. Interventions (see Table 2 below) are derived from standard approaches of addiction treatment, mainly Relapse Prevention (114), CBT (42) and to a lesser extent mindfulness (115). In order to improve compliance/acceptability, usability was evaluated among a sample of end-users and clinicians on a first version of the app, and changes in the functionality of the app were made on an as-needed basis.

**Table 2 tab2:** Types and number of interventions proposed by the Craving-Manager app according to the Behavior Change Techniques taxonomy (96).

Code	Type of intervention according to the BCT taxonomy	Number of interventions
1.2	Problem solving/ coping planning	6
1.3	Goal setting (outcome)	1
1.4	Action planning	1
1.7	Review of outcome goals	1
2.2	Feedback on behavior	1
2.3	Self-monitoring of behavior	6
3.1	Social support (general)	1
3.3	Social support (emotional)	1
4.1	Instruction on how to perform a behavior	1
4.3	Reattribution	2
9.2	Pros and cons	3
11.2	Regulation of negative emotions	2
11.3	Conserving mental resources	2
12.3	Antecedents	3
12.4	Distraction	1
15.1	Verbal persuasion to boost self-efficacy	2

The app begins with an initial questionnaire for systematic assessment of DSM-5 diagnosis for all substance and behavioral addictions (6). The app then collects the primary (i.e., main problematic) addiction(s), on which the app will be focused, according to participant’s demand and current diagnosis. In the full app version dedicated to the Experimental Group, person-specific cues are also explored (37) for further personalization of EMA questionnaires, and at-risk locations, i.e., previously associated with addictive use or craving, are identified on a map. In this full app version, supportive/protective factors (such as family/friends or pleasant activities to distract from craving,) but also participant perceived disadvantages of continued use, and on the contrary, participant perceived benefits of quitting, are collected for personalization of further support/intervention EMI messages. Participants receiving the full version of the app will also receive informational contents about the definition of addiction and craving, delivered by an Embodied Conversational Agent (ECA) (101, 116, 117).

During the 4-week use of the app, participants from both groups are prompted with 4 daily EMA questionnaires (5 min each), randomized across the day in a time slot of 14 h. Electronic interviews assess the presence of cues, craving or addictive use, since the previous assessment, for the primary addiction(s), as well as a list of mood states, and use of other substances or addictive behaviors. In the Experimental group only, an EMI is immediately proposed to participants who report exposure to cues, craving, or addictive use (Table 3). In this group, additional EMI is also proposed on demand, or when the app detects that the participant is approaching a place previously marked as at-risk on the map, thanks to continuous geolocation collected at a rate of 0.2 Hz. Each time cues, craving or addictive use are reported, the participant has the possibility to add new cues/at-risk locations or situations in the registered list for further monitoring.

**Table 3 tab3:** Framework’s resume of the Craving-Manager app functioning.

Situation	Decision rules	Decision point	Tailoring variables	Intervention options (IO)* according to BCT Taxonomy (see Table 2)
Addictive use report	IF use = TRUE since the previous assessment AND participant consents THEN see IO column.	Daily EMA prompt	Addictive use Type of substance use/addictive behavior Participant acceptance	1.2/1.3/ 2.3 + 12.3 /3.3/ 4.3 + 1.4/ 9.2/11.3 + 11.2 /12.4 /15.1
Craving report	IF level of craving is ≥4 (out of 7) OR IF level of craving is > last week’s mean level of craving AND participant consents THEN see IO column	Daily EMA prompt	Level of craving Type of substance use/addictive behavior Participant acceptance	1.2/2.3 + 12.3/2.3 + 1.2/3.3/4.1/9.2/11.3 + 11.2 /12.4
Cues report	IF exposition to a cue = TRUE AND participant consents THEN see IO column	Daily EMA prompt	Being exposed to a cue Participant acceptance	1.2/2.3 + 1.2/3.3 /11.3 + 11.2/12.4
At-risk location detected (GPS)	IF distance < fixed distance (10–90 meters) around one of the at-risk location points AND IF participant consents THEN see IO column.	Anytime, when detected	Distance to at-risk location Participant acceptance	1.2/2.3 + 1.2/3.3 /11.3 + 11.2 /12.4
On-demand help request	IF click on the help button AND report: risk of use, use, craving, exposition to a cue THEN see IO column.	Anytime, on participant’s demand	Individual’s need Type of situation reported	1.2/1.3/2.3 + 1.2/2.3 + 12.3/3.3/4.1/4.3 + 1.4 9.2/11.3 + 11.2/12.4/15.1

*When several options are possible, the intervention is drawn at random, using a draw without discount rule, to maximize alternation of intervention options, and avoid fatigue effects.

A list of types of intervention proposed by the app is described in Table 2 according to the Behavior Change Techniques (BCT) taxonomy (96). Among the Craving-Manager interventions, the most frequent types are Problem solving/ coping planning [1.2] interventions that aim to help to manage situations that could lead to addictive use, Feedback and Self-monitoring [2.2–2.3] interventions that aim to guide user to be more aware and focused on his/her environment and its triggers to some problematic behaviors, Pros and cons [9.2] interventions that are reminders regarding negatives consequences of addictive use and benefits from quitting, and Antecedents [12.3] interventions suggest ways to avoid cue exposure drawing from past experiences.

At the end of each week, participants in the Experimental group receive a personalized feedback about cues encountered, craving and addictive use across the past 7 days, and motivational messages to encourage effort to reduce/quit primary addiction(s). Attention is also drawn to other substances/addictive behaviors, in order to avoid the risk of switching addiction (118). The app also monitors evolution of self-efficacy, and presents a graph of EMA response rates to encourage completion. The control group only receives feedback on the EMA completion rate.

The functioning of the app is described in Table 3 according the Nahum-Shani and colleagues list of contents and design principles of JITAI (92). *Decision points* are the moment when the choice of an intervention can be done. *Decision rules* determines whether or not an intervention is proposed, and which one, among *Intervention Options* (IO), thanks to an examination of *Tailoring variables*.

### Analysis strategy

2.8.

The primary objective to evaluate the efficacy of the Craving-Manager app over 4 weeks, as compared to a restricted (placebo) version of the app, will be assessed by comparing the percentage of participants for whom a 20% decrease in frequency of use of primary substance/ addictive behavior was observed, between the 1st and 4th week of smartphone app use, in the experimental group versus the control group. This 20% reduction threshold was defined in line with decrease in the “percentage of using days” observed with smartphone apps targeting alcohol (75) and substance use disorders (80).

Analyses will be conducted according to the intent to treat principle, in which all randomized participants will be included in the group in which they were first randomized and all their data will be used, regardless of the changes over the study duration.

In addition, in case some participants stopped using the app before the expected termination, a sensitivity analysis will be performed using the LOCF (Last Observation Carried Forward) approach, to calculate the decrease in frequency of use of primary substance/behavior not on the 4^th^ week, but on the last 7 days with at least one EMA questionnaire completed.

The comparison between groups will focus on the proportion of participants that reach a 20% decrease in use of primary substance(s)/ addictive behavior(s). This is a superiority trial (bilateral test). The 95% confidence intervals (exact binomial distribution) in each group will be calculated. These 2 proportions will be compared with a Chi2 test or with Fisher’s exact test, according to the size of the expected values under the hypothesis of independence. Mixed effects logistic regression model will be used to adjust stratification factor (random effect on centers) and other major confounding factors. Assumption of the models (log-linearity of the associations) will be systematically checked.

Efficacy of the intervention will also be examined on secondary endpoints: Multifactorial addiction severity (assessed with ASI Composite Score for the primary addiction) at 1-month and 4-month follow-ups, and craving self-reported in the last EMA week, and reported at 1-month and 4-month follow-ups in the Craving Evaluation Scale.

Further analysis will explore factors associated with efficacy, among initial severity of addiction (ASI Composite Score for the primary addiction at inclusion), initial craving frequency and intensity (with Craving Evaluation scale), type of addiction, comorbid psychiatric disorders, and past or concomitant addiction treatment. Temporal evolution of craving and substance use/addictive behaviors over the 4 weeks of app use will be described.

Feasibility, acceptability and intervention satisfaction will be assessed at the one-month follow-up by the number of days and frequency of use of the app (calculated from EMA responses: number of questionnaires answered on total number of questionnaires proposed by the app), with acceptability questionnaires (AES, uMARS and D-WAI) and with the specific CSQ-8 questionnaire assessing intervention satisfaction, rate of participants who did not finish the study, and reasons for stopping.

Impact of the 4 weeks use of the app on subsequent treatment will be assessed at 4-month follow-up with the rate of first-time attendance to the standard treatment, time to first-time attendance to the standard treatment, compliance with standard treatment (TSR), and evolution of severity of addiction during the standard treatment (ASI Composite Score).

Reliability of the app to diagnose addictive disorders will be examined by comparison with diagnosis explored at inclusion with MINI (human interview).

The quantitative variables will be compared by Student t test if the conditions of validity are respected (normal distribution, homogeneous variances). If the variances are different between both groups, we will use Student t test for unequal variances; if the distribution is not normal, we will use non-parametric Wilcoxon test. Mixed effects linear regression models will be used to adjust on stratification factor (random effect on centers) and other major confounding factors. Assumptions of the models (normal distribution, homogeneous variances, linearity of the associations) will be systematically checked. In some cases, it may be necessary to transform or recode some variables to adapt them to the conditions under which statistical tests are applied.

Statistical analysis will be performed using JMP Pro 16.0 (SAS Institute, Cary, North Carolina), and HLM software 8.0 (Scientific Software International) for mixed effects linear regression models. For all the tests, the level of significance will be set at *p* < 0.05.

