### Study procedure and intervention

2.6.

Participants will be recruited among patients on a waiting list for a first clinical appointment at the inclusion center, with at least 1-month delay before the first scheduled appointment (to avoid overlap of the intervention proposed by the Craving-Manager app with the intervention that will be provided later by the addiction clinic; Figure 1). First, a telephone screening interview will allow to explain the study and to check the main inclusion criteria. Then, interested and eligible participants will receive an inclusion visit (baseline) at the inclusion center to sign the informed consent, and receive a face-to-face research interview, with ASI, MINI, TSR and Craving Evaluation scale (see Table 1).

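### For the secondary ASI and Craving Evaluation outcomes, the plan does not name the M0 score as a covariate or say whether the test or the model is the main analysis

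*Protocol article*

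**What the plan says.** All references are to the protocol article.

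- **Endpoints (2.8 Analysis strategy).** One secondary efficacy endpoint is severity: "Multifactorial addiction severity (assessed with ASI Composite Score for the primary addiction) at 1-month and 4-month follow-ups". The other concerns craving, taken both from the app and from the interviews: "craving self-reported in the last EMA week, and reported at 1-month and 4-month follow-ups in the Craving Evaluation Scale".
- **Baseline data (2.6 Study procedure and intervention; Table 1).** At the inclusion visit participants "receive a face-to-face research interview, with ASI, MINI, TSR and Craving Evaluation scale". Table 1 schedules the ASI and the craving scale at M0, M1 and M4.
- **Comparison of quantitative variables (2.8).** The default rule reads: "The quantitative variables will be compared by Student t test if the conditions of validity are respected (normal distribution, homogeneous variances". When the variances differ, the unequal-variance version takes its place. Departure from normality moves the comparison to ranks: "if the distribution is not normal, we will use non-parametric Wilcoxon test".
- **Adjusted model (2.8).** A regression model is planned beside these tests: "Mixed effects linear regression models will be used to adjust on stratification factor (random effect on centers) and other major confounding factors". The confounders are not listed.
- **Stated use of the M0 scores (2.8).** They appear among the factors to be explored for association with efficacy: "initial severity of addiction (ASI Composite Score for the primary addiction at inclusion), initial craving frequency and intensity (with Craving Evaluation scale".

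The article neither names the M0 score as a covariate in the comparison of the arms nor excludes it. It does not say which of test and model is the main analysis for these outcomes.

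**The concern.** The ASI Composite Score and the Craving Evaluation scale are each measured three times in the same person. When a randomised comparison concerns the M1 or M4 value, the M0 value of the same scale is usually the strongest available predictor of it. The test that the plan describes makes no use of it. Any substance or behavioural addiction is eligible, so severity at entry is likely to vary widely, and an unadjusted test leaves that variation in the error term.

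The reported quantity is also left open. A t test or linear model gives a mean difference on the scale. A Wilcoxon test gives a rank comparison and no such difference. The data decide which one appears, the mixed model stands beside it, and variables may be transformed or recoded. All are read at p < 0.05 with no stated order. A reader of the results could not tell from the plan which figure was meant to answer the question.

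At stake are the power and interpretability of the secondary efficacy results. The sample size was set for the binary primary endpoint, so these outcomes have only the precision that the analysis can give them.

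**Working it through.** **1. The plan's own figure.** The article gives a sample size only for the primary endpoint: 137 per arm for 20% vs. 5%, 90% power, two-sided 5%, 20% loss to follow-up (2.3). The usual two-proportion formula gives 101 per arm without continuity correction. With the correction:

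101/4 × [1 + √(1 + 4/(101 × 0.15))]² = 113.9, so 114; and 114 × 1.2 = 136.8, so 137.

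The figure reproduces, and the present point does not affect it.

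**2. Inputs for the secondary outcomes.**
- Analysed per arm: 137 × 0.8 = 109.6, taken as 109. Applying the 20% loss to the M1 and M4 interviews is an assumption.
- Two-sided 5% and 80% power: 1.960 + 0.842 = 2.802.
- Correlation r between the M0 and follow-up value of the same scale: not in the document. Assumed 0.3, 0.5 and 0.7.
- Standard deviations and expected effects: not in the document. Results are therefore in SD units.

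**3. Formulas.** Adjusting for M0 multiplies the residual variance by 1 − r². The detectable difference is 2.802 × √(2/109) × √(1 − r²) in SD units. Without M0 it is 2.802 × 0.1355 = 0.38. Power for an assumed difference of 0.3 SD is Φ(0.3 / [0.1355 × √(1 − r²)] − 1.960). Without M0 it is Φ(2.215 − 1.960) = 60%.

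| Analysis | Variance reduction | Detectable difference (80% power) | Power at 0.3 SD | N per arm for 0.3 SD, 80% power |
|---|---|---|---|---|
| Follow-up value only | 0 | 0.38 SD | 60% | 175 |
| With M0, r = 0.3 | 9% | 0.36 SD | 64% | 159 |
| With M0, r = 0.5 | 25% | 0.33 SD | 73% | 131 |
| With M0, r = 0.7 | 49% | 0.27 SD | 87% | 89 |

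**4. Does the switch between tests inflate the error rate?** The rule was simulated with 109 per arm and no true difference, in 4,000 runs (Monte Carlo standard error about 0.35 percentage points). A Shapiro-Wilk check in each arm decided on Wilcoxon, and a Levene check decided between the two t tests.

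| Data | Rule as planned | Unequal-variance t test alone |
|---|---|---|
| Normal | 4.5% | 4.4% |
| Lognormal | 5.1% | 5.3% |

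There is no material inflation. With normal data the rule still moved to Wilcoxon in about 10% of runs, and with lognormal data in all of them. So the switch changes what is estimated, not the error rate.

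**The case against.** The strongest reply is that the plan does contain an adjusted model, and that its unlisted confounders may well include the M0 score. If they do, the gain over the plan's own model is zero. An article may leave a covariate list to the full protocol or SAP, which were not available for this review. The sentence on tests is also generic. It covers measures with no M0 value, such as the acceptability and satisfaction questionnaires, and does not say whether the follow-up value or the change is tested. This stands as a limit on the claim. It does not remove it: the article states a method for these outcomes, that method is unadjusted, and the place of the model beside it is not given.

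A reader might infer more than the text supports:

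- **That the M0 scores are discarded.** Nothing says so. They are used in the exploratory analysis, and the evolution of the ASI score during standard treatment is also planned.
- **That the model contains centre only.** It also includes other confounders, unnamed.
- **That participants who miss M1 or M4 are dropped visit by visit.** Missing-data handling for the secondary outcomes is not described. Section 2.8 states intention to treat, with all data of all randomised participants used.
- **That chance imbalance at M0 biases the result.** Under randomisation the unadjusted comparison is valid, and its standard error already allows for such imbalance.
- **That every craving outcome has its own M0 value.** EMA craving is scored out of 7 (Table 3) and collected only in the app. The Craving Evaluation scale rates intensity from 0 to 10 (2.5).

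Separate analyses at M1 and M4 are also legitimate; a joint model is an option, not a requirement.

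**Conclusion.** The point holds in a limited form. For the ASI Composite Score and the Craving Evaluation scale, the stated comparison makes no use of the M0 value, the adjusted model does not name it, and neither the main analysis nor the effect measure is fixed in advance. The loss is in precision and clarity, not validity.

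Its size depends on the assumed correlation. From r = 0.3 to 0.7 the variance falls by 9% to 49%, which is worth a sample 1.10 to 1.96 times as large, from 1/(1 − r²). At the low end the gain is small. The figures further assume about 109 analysed per arm and that the unadjusted result would otherwise lead. The outcomes are secondary, and the primary analysis and the total of 274 are untouched. The change is worth making because it uses data already scheduled.

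**What to change.** In section 2.8, or in the SAP if it does not already say so, and before any comparison by arm:

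1. For the ASI Composite Score and the Craving Evaluation scale, name the already planned mixed linear model as the main analysis, with arm, the M0 value of the same measure, and centre. M1 and M4 may be modelled jointly, with arm by visit and a participant effect.
2. Report the adjusted mean difference with its 95% confidence interval at each visit.
3. Keep the Wilcoxon test and transformed analyses as sensitivity analyses, so that distribution checks no longer choose the headline result.
4. List the other confounders.
5. For craving in the last EMA week, state that no same-scale M0 value exists. The M0 Craving Evaluation score may serve as a proxy covariate only, and its correlation with EMA craving is unknown.

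The cost is wording. Both scales are already scheduled at M0, M1 and M4, and software for mixed linear models is already named. No visit, participant or measurement is added.

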### Sample size calculation

2.3.

A power analysis was performed to determine the sample size based on data from a previous EMA study among subjects beginning outpatient addiction treatment (101). We considered that a significant clinical effect was a decrease of at least 20% of addictive use frequency for 20% of the participants in the experimental group between the 1st and 4th week of smartphone app use. We expect that 5% of participants in the control group will present this decrease. To observe a difference of 15% (20% vs. 5%), with a 90% statistical power, a type 1 error rate of 5% and assuming 20% loss-to-follow-up (considered as failures), we need 137 participants randomized to each group (274 participants to be included in total).

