### Randomization and blinding

2.4.

Participants will be randomized in two distinct groups: the Experimental Group will have access to the full active version of the Craving-Manager app (EMA and EMI) during 1 month, and the Control Group will have access to a restricted (placebo) smartphone app (EMA only) during 1 month.

Randomization will be done by the app, and will take place after confirmation of eligibility and the informed consent procedure. It will be done centrally in a 1:1 ratio, and stratified by inclusion center.

Participants will be unaware of the specific goals of the study or of the differences between the 2 versions of the app. The primary endpoint will be collected through EMA. Research staff will be unaware of group assignment and secondary endpoint collected through face-to-face interviews will be assessed blindly to the randomization group.

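### ASI and craving secondary endpoints: the first-line test ignores the baseline score, and the plan neither names that score as a covariate nor says whether the test or the mixed model is the main analysis

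*Protocol article*

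**What the plan says.** Protocol article, section 2.8 (Analysis strategy), names as a secondary efficacy endpoint "Multifactorial addiction severity (assessed with ASI Composite Score for the primary addiction) at 1-month and 4-month follow-ups". It adds craving in the last EMA week and craving on the Craving Evaluation scale at the same two follow-ups. All are stated as levels at follow-up; none is defined as a change from baseline.

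For analysis, the section says that "The quantitative variables will be compared by Student t test if the conditions of validity are respected". Unequal variances lead to the unequal-variance t test and non-normality to the Wilcoxon test. It then adds: "Mixed effects linear regression models will be used to adjust on stratification factor (random effect on centers) and other major confounding factors". The confounders are not listed, and nothing says whether the test or the model carries the conclusion.

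Section 2.6 and Table 1 place the ASI and the Craving Evaluation scale at the baseline visit (M0). The only analysis role that section 2.8 names for those baseline values is exploratory, among possible factors associated with efficacy: "initial severity of addiction (ASI Composite Score for the primary addiction at inclusion), initial craving frequency and intensity".

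**The concern.** A t, Welch or Wilcoxon test on the follow-up value cannot use the baseline value of the same score. That value is usually among the strongest predictors of the follow-up value, and it is already in hand. Leaving it out widens the confidence interval for no saving.

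The mixed model does not settle the matter as worded. In a randomised trial a baseline score is a prognostic covariate and not strictly a confounder, so a promise to adjust for confounders does not commit anyone to including it. Even if it is included, the reader cannot tell whether the adjusted or the unadjusted result is to be the main one. At stake is the precision of the ASI and craving results, and clarity about which estimate counts for each endpoint.

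**Working it through.** **The plan's own figure.** Section 2.3 gives 137 per group for the binary primary endpoint (20% vs 5%, 90% power, 5% type 1 error, 20% loss). The two-sided continuity-corrected formula gives 114 per group, and 114 × 1.2 = 136.8, rounded up to 137. The figure therefore reproduces. It concerns only the primary endpoint; the article states no SD, effect size or power for ASI or craving.

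**Inputs for the secondary endpoints.**
- Per arm with a follow-up score: 137 × 0.8 = 109.6, taken as 110. This assumes that the 20% loss in section 2.3 also applies at the 1- and 4-month visits.
- Allocation 1:1 (section 2.4); two-sided 5% (section 2.8).
- Correlation r between the baseline and follow-up score: not in the document. It is an assumption, shown from 0.2 to 0.7.

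**Formulae**, in units of the follow-up SD:
- Unadjusted: SE = √(2/110) = 0.135.
- Adjusted for baseline: SE = √(2(1 − r²)/110).
- Detectable difference at 80% power = 2.802 × SE. Unadjusted: 2.802 × 0.1348 = 0.38.
- Power for an illustrative 0.35 SD effect = Φ(0.35/SE − 1.96). Unadjusted: Φ(0.64) = 74%.
- Relative sample size that the unadjusted test would need for the same precision = 1/(1 − r²).

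| r | Variance removed (r²) | Detectable difference (SD) | Power at 0.35 SD | Extra participants equivalent |
|---|---|---|---|---|
| unadjusted | – | 0.38 | 74% | – |
| 0.2 | 4% | 0.37 | 75% | 4% |
| 0.3 | 9% | 0.36 | 78% | 10% |
| 0.4 | 16% | 0.35 | 81% | 19% |
| 0.5 | 25% | 0.33 | 85% | 33% |
| 0.6 | 36% | 0.30 | 90% | 56% |
| 0.7 | 49% | 0.27 | 95% | 96% |

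With no loss (137 per arm) the unadjusted SE is √(2/137) = 0.121 and the detectable difference is 0.338 SD. The percentage gains are the same, because they depend only on r.

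**Chance baseline imbalance.** The variance of the unadjusted difference splits as 2/110 = (1 − r²)(2/110) + r²(2/110). The second term is the contribution of chance baseline differences between arms. It is exactly the part that adjustment removes, and the unadjusted standard error already contains it. It is the same loss seen from another side and should not be counted twice.

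**The case against.** The strongest reply is that adjustment is already planned. The mixed linear model comes shortly after the test rule in the same paragraph, and its confounding factors may be prognostic covariates loosely named. The commitment to check linearity of associations also makes most sense if continuous covariates enter. This stands in part. A reader might infer that the plan rules out baseline adjustment and will report only raw follow-up contrasts; the document does not say that. What it lacks is a commitment to the baseline score and a statement of which analysis leads.

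A second reply is that a covariate list belongs in the SAP or full protocol, which are not shown. That would answer a complaint about silence. Here the article itself states an unadjusted first-line test and leaves its rank against the model open.

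Third, the test rule is generic. It also covers AES, uMARS, D-WAI, CSQ-8 and app use, which have no baseline and for which a two-sample test is reasonable. This is right, and the fix respects it.

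Fourth, not every endpoint has its own baseline. EMA runs only during app use, after randomisation, and Table 3 scores EMA craving out of 7. The M0 craving scale runs from 0 to 10 and covers the past 30 days (section 2.5). So last-week EMA craving has only a proxy covariate, and the table above cannot be assumed to apply to it.

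Fifth, the size rests on an assumed r. By 4 months some participants may have started standard treatment, which could weaken the correlation. At r of 0.2 to 0.3 the gain is worth only 4% to 10% in sample size. This also stands.

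**Conclusion.** The point holds as a free improvement to the secondary analyses. The stated first-line comparison for ASI and craving uses no baseline information. The planned model could use it, but is neither committed to doing so nor named as the main analysis. If the first-line test is followed, the variance reduction forgone is 9% to 49% for r of 0.3 to 0.7. The detectable difference at 110 per arm is then 0.38 SD where it could be between 0.36 and 0.27 SD. These figures assume a linear relation with the baseline score, the same r in both arms, and 20% loss at the follow-up visits.

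A reader might also infer that chance baseline imbalance biases the unadjusted comparison or inflates its error rate. It does not: under randomisation the unadjusted test is valid, and its standard error already allows for such imbalance. The primary endpoint and the 274 participants are not touched.

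**What to change.** In section 2.8, or in the SAP with a matching sentence in 2.8:

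- Make the mixed linear model already planned the main analysis for the ASI Composite Score and the Craving Evaluation scale at 1 and 4 months. Include arm, the M0 value of the same score, and centre as now planned. Report the adjusted difference with a 95% confidence interval.
- For craving in the last EMA week, use the M0 Craving Evaluation intensity as a proxy covariate, and expect a smaller gain.
- Keep the t, Welch or Wilcoxon test as supportive for these endpoints, and as the test for measures with no baseline (AES, uMARS, D-WAI, CSQ-8, app use).

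The cost is wording only. The covariates are already collected and the mixed model is already planned, so no participants, visits or measurements are added. The change should be made before unblinded data are seen.
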